### EHR Alert

The EHR alert will fire when a clinician orders normal saline in a patient with group D sepsis who is randomized to the intervention arm. The alert will announce that there is evidence for a reduced mortality risk from use of balanced crystalloids in this patient and will ask the clinician to choose either lactated Ringers or PlasmaLyte (Baxter), unless there is a clinical indication to continue normal saline. The alert will fire on normal saline orders for maintenance infusions and boluses, but not on normal saline ordered as part of medication diluents and carrier fluid for intravenous medications.

### Outcomes

The primary outcome is 30-day inpatient mortality. Secondary outcomes include ICU admission, in-hospital mortality, receipt of vasoactive drugs, receipt of new kidney replacement therapy, and receipt of mechanical ventilation (vasoactive drugs, kidney replacement therapy, and mechanical ventilation are counted if they occur after randomization and within the 30-day study period). Process outcomes include volume of normal saline and percentage of alerts accepted.

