### Population

All adults (aged ≥18 years) presenting to study EDs will be screened. Inclusion criteria are (1) blood culture order in the ED, (2) classification as group D by the vital signs trajectory algorithm, and (3) clinician-initiated normal saline order. Patients who meet the inclusion criteria will be randomized to intervention vs usual care. If study patients are discharged and readmitted to a study hospital during the study period, they will be eligible for reenrollment (Figure 3).

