### Randomization and Allocation

Patients will be randomized to usual care vs intervention using software within the EHR in a simple 1:1 ratio without stratification. Randomization occurs at the point of clinicians initiating a normal saline order.

For patients randomized to the intervention arm, the EHR alert will fire in the ED and the ICU every time normal saline is ordered until the first of the following events: ICU discharge, death, or 30 days of hospitalization. The study intervention will not be continued in the wards. For patients randomized to the usual care arm, there will be no EHR alert in response to fluid orders.

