### Data Management

Given the EHR-embedded nature of this pragmatic trial, data collection will occur through EHR data extraction, and all data will be routinely collected information, including demographic characteristics, vital signs, laboratory values, medication orders, and vital sign status at hospital discharge. At the end of every study month, data will be extracted for all patients that month who were randomized. Baseline variables, liters of crystalloid fluids administered, and outcomes will be collected on all randomized patients. After study completion, there will be an additional data extraction completed at 1 month following study completion to finalize patient data. If any patient remains hospitalized at the end of the 1-month period following study completion, the patient’s in-hospital mortality status will be documented as incomplete. No other instances of missing outcomes data or loss to follow-up are expected, as all data will be extracted from the EHR. Monthly hospital-level aggregate reports will be sent to the DSMB by allocation group to allow evaluation of crystalloid fluid distribution, without information on outcomes. At the interim analyses, a detailed patient-level report will be sent to the DSMB unblinded to allocation with information on outcomes (Table 2).

**Table 2. zoi241019t2:** Template for Patient-Level Data for Enrolled Patients in the Precision Resuscitation With Crystalloids in Sepsis (PRECISE) Trial

Pt	Admission date	Randomization	ICU^a^	Baseline variables^b^	NS^c^	BC^c^	30-d mortality	In-hospital mortality^d^
1	MM/DD/YY	Intervention	No	Variable	NS value	BC volume	Rate	Rate
2	MM/DD/YY	Intervention	Yes	Variable	NS value	BC volume	Rate	Rate
3	MM/DD/YY	Usual care	Yes	Variable	NS value	BC volume	Rate	Rate
4	MM/DD/YY	Intervention	Yes	Variable	NS value	BC volume	Rate	Rate
5	MM/DD/YY	Usual care	Yes	Variable	NS value	BC volume	Rate	Rate
6	MM/DD/YY	Usual care	No	Variable	NS value	BC volume	Rate	Rate
7	MM/DD/YY	Usual care	No	Variable	NS value	BC volume	Rate	Rate
8	MM/DD/YY	Intervention	Yes	Variable	NS value	BC volume	Rate	Rate

Abbreviations: BC, balanced crystalloids; ICU, intensive care unit; MM/DD/YY, month, day, year; NS, normal saline; Pt, patient identifier.

^a^
If patient was admitted from the emergency department to an ICU.

^b^
There will be individual columns, including baseline variables such as age, sex, race and ethnicity, hospital, and Sequential Organ Failure Assessment score.

^c^

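### Vasoactive drugs, ventilation and ICU admission are not clearly limited to care that starts after randomization, so these secondary effects may be diluted.

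*Protocol article*

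**What the plan says.** The Outcomes section of the protocol article lists five secondary outcomes: "Secondary outcomes include ICU admission, in-hospital mortality, receipt of vasoactive drugs, receipt of new kidney replacement therapy, and receipt of mechanical ventilation". The word *new* is attached to kidney replacement therapy alone.

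A timing rule follows in parentheses: "vasoactive drugs, kidney replacement therapy, and mechanical ventilation are counted if they occur after randomization and within the 30-day study period". It covers three of the five outcomes. ICU admission is not among them.

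On when randomization happens, Randomization and Allocation states: "Randomization occurs at the point of clinicians initiating a normal saline order". No location is given. The inclusion criteria under Population are "1) blood culture order in the ED, (2) classification as group D by the vital signs trajectory algorithm, and (3) clinician-initiated normal saline order". The ED is tied to the blood culture, not to the saline order. For patients already allocated to intervention, "the EHR alert will fire in the ED and the ICU every time normal saline is ordered".

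Two other places bear on ICU admission. The footnote to the ICU column of Table 2 (Data Management) reads "If patient was admitted from the emergency department to an ICU". Statistical Analysis also plans an analysis of the ICU-admitted subset on the footing that these patients could meet the alert in both settings.

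**The concern.** For vasoactive drugs and ventilation the outcome is receipt. A patient on a vasopressor before the saline order and still on it an hour later has received it after randomization. Under that reading the event was settled before allocation, and the alert could not have prevented it.

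For ICU admission there is no time anchor at all. If a patient's first normal saline order is placed in the ICU, admission precedes randomization. Nothing in Population or in Randomization and Allocation rules this out.

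Two analysts could build different endpoints from this text. The broader version would understate any true benefit on up to three of the five secondary outcomes. It would equally understate any true harm, which matters because Safety End Points evaluates adverse events through the primary and secondary outcomes. The Introduction describes group D patients as hypotensive, so vasoactive treatment before the first saline order is plausible, though the article gives no figure for it.

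**Working it through.** **The plan's own figure.** The article gives no rate, effect or power for any secondary outcome. The only figure to anchor on is the sample size for mortality in Table 1: 6% vs 3%, two-sided 0.05, 90% power, 1001 per arm. A two-proportion calculation with pooled variance and no continuity correction gives 1002 per arm, which agrees within rounding. This size is used below only as the number per arm. It rests on mortality and does not change with this point.

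**Reading the text.**
1. Support that ended before randomization is excluded by the timing rule.
2. Kidney replacement therapy already in place is excluded by the word *new*.
3. Vasoactive drugs or ventilation started before randomization and still running are excluded if *occur* means onset, and included if it means receipt. The text does not settle which.
4. ICU admission before randomization is covered by no rule.

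**Effect of counting care already in place.** Let q be the share already receiving the support at randomization. By randomization q is the same in both arms in expectation. Suppose all these patients are counted. With new-onset risks c (usual care) and t (intervention) among the rest:

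- usual care risk = q + (1 − q)c
- intervention risk = q + (1 − q)t
- risk difference = (1 − q)(c − t)
- relative risk = [q + (1 − q)t] / [q + (1 − q)c], which lies closer to 1 than t/c whenever q > 0 and t ≠ c

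If t = c, the two risks are equal for any q, so there is no bias under the null.

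**Illustration (assumptions, not figures from the article).** c = 12% and t = 8%, so the relative risk is 0.08/0.12 = 0.67. Power is for a two-sided 0.05 pooled z test without continuity correction, at 1001 per arm when everyone is counted and at 1001 × (1 − q) per arm for new onset only.

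| q | Usual care risk | Intervention risk | Difference (points) | RR | Power, all counted | Power, new onset only |
|---|---|---|---|---|---|---|
| 0% | 12.0% | 8.0% | 4.0 | 0.67 | 85% | 85% |
| 2% | 13.8% | 9.8% | 3.9 | 0.72 | 78% | 84% |
| 5% | 16.4% | 12.6% | 3.8 | 0.77 | 68% | 83% |
| 10% | 20.8% | 17.2% | 3.6 | 0.83 | 54% | 81% |

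Worked line for q = 10%: 0.10 + 0.90 × 0.12 = 0.208; 0.10 + 0.90 × 0.08 = 0.172; 0.172/0.208 = 0.83.

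**Second set of assumptions.** With c = 20% and t = 16% (RR 0.80), q = 5% gives RR 0.84 and q = 10% gives RR 0.87. Power is 54% and 45% with ongoing support counted, against 62% and 60% for new onset only. The direction is the same; the size depends on q and on the event rate.

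**What adjustment does.** The secondary model in Statistical Analysis includes the SOFA score at randomization. That is a covariate. It does not take patients already on support out of the event count, so it does not remove the dilution.

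No figure is offered for ICU admission, because the article gives no basis for the share of admissions that precede randomization.

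**The case against.** **The timing rule is already a post-randomization rule.** Read as onset, it excludes ongoing support. The word *new* may have been added to kidney replacement therapy only because chronic dialysis would otherwise persist through any window. Its absence elsewhere then shows no intent to count running vasopressors or ventilators. This stands in part: a reader might infer that the plan prescribes counting prior care, and the text does not support that. It is an ambiguity in a stated rule.

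**Enrollment is described as an ED process.** Algorithm Description says patients are classified rapidly in the ED because fluids start early. The ICU subset analysis presumes exposure in the ED first, and Table 2 treats ICU admission as a move from the ED. The alert's firing in the ICU is described for patients already allocated. This also stands in part: ICU admission will normally follow randomization, and a reader should not infer that a sizeable share precedes it. But no criterion confines the saline order to the ED, and vasoactive treatment or intubation can precede that order within the ED itself.

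**Receipt after randomization in all randomized patients is a legitimate intention-to-treat measure.** True, and it can be kept. It answers a less sensitive question.

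**An article condenses the protocol.** Detailed time-stamp logic may well sit in the full protocol. But the article does state a counting rule, applies *new* to one of three supports, and leaves ICU admission out of the rule. The wording of that rule is what is at issue.

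**Conclusion.** The point holds as an ambiguity with a known direction. As worded, vasoactive drugs and ventilation already running at randomization can be counted, and ICU admission has no time anchor. If such care is counted, the risk difference shrinks by the factor (1 − q) and the relative risk moves toward 1.

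The size cannot be derived from the article. Under the assumed 12% vs 8% and q of 2% to 10%, a relative risk of 0.67 reads 0.72 to 0.83. If few patients are on support at the triggering order, the dilution is small.

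A reader might take the power column above as a shortfall in the plan. It is not: the plan makes no power claim for secondary outcomes, and the primary outcome, its sample size and its error rate are untouched. This is a worthwhile and cheap improvement to the secondary endpoints.

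**What to change.** - Define vasoactive drugs and mechanical ventilation as new onset after randomization and within the 30-day study period, among patients not receiving them at randomization, in line with kidney replacement therapy.
- Count ICU admission only when it occurs after randomization, among patients not already in an ICU.
- Report by arm the number already receiving each support, or already in an ICU, at randomization.
- Keep receipt after randomization in all randomized patients as a supportive analysis, if wanted.

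Status at randomization is a baseline characteristic, so restricting to patients not yet on support keeps the randomized comparison valid. The cost is a change of wording, time-stamp logic in the EHR extract, and slightly smaller denominators for these outcomes. At q = 5%, for example, about 951 of 1001 per arm remain (1001 × 0.95). The sample size does not change.

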### Statistical Analysis

The primary outcome is 30-day inpatient mortality compared between the usual care and intervention arms using intention-to-treat analysis (ie, all patients randomized to intervention vs usual care regardless of whether the intervention resulted in a change in fluid choice). The outcome of 30-day inpatient mortality is measured for the index hospitalization. Readmissions and subsequent deaths are not counted toward the primary outcome for the initial hospitalization, but are considered for the readmission hospitalization. The primary analysis will be an assessment for a difference in 30-day inpatient mortality between the arms with a 2-sided *z* test with continuity correction and pooled variance. Thirty-day inpatient mortality rates will be determined using 95% CIs within each study arm and for the observed difference between study arms.

The secondary analysis for primary and secondary outcomes will be a generalized mixed-effects linear model (ie, log-binomial regression model) to estimate the outcome, adjusted for baseline characteristics including age, sex, race and ethnicity, and Sequential Organ Failure Assessment (SOFA) score at randomization. Race and ethnicity will be included in the analyses given potential disparities in treatments and health outcomes by race. The model will also be adjusted for month of the trial, with an interaction term between month and treatment allocation, to evaluate for temporal trends in the efficacy of the intervention (eg, increasing use of balanced crystalloids in usual care could result in decreased separation of the study arms). The hospital to which the patient is admitted will be defined as a random effect (random intercept) in the mixed model. In a separate sensitivity analysis, the hospital to which the patient is admitted will be defined as a fixed effect to evaluate the robustness of the findings. The covariate-adjusted 30-day inpatient mortality rates will be determined using 95% CIs for each study cohort and for the observed difference between the usual care and intervention arms in 30-day inpatient mortality rates. Relative risks will be calculated to measure the degree of association between individual risk factors and 30-day inpatient mortality. The SAS GLIMMIX Procedure, version 9.4 (SAS Institute Inc) will be used to implement the log-binomial regression model.

The process outcome of volume of normal saline administered per patient will be compared in unadjusted analysis between the intervention and usual care arms. The total number of alerts generated and the percentage of alerts accepted in the intervention arm will be reported.

Secondary analysis of the primary outcome will be performed on the subset of randomized patients who were admitted to the ICU and thus would have potential exposure to intervention in both the ED and ICU settings. Any additional outcomes or analyses will be clearly identified as post hoc and will be considered hypothesis-generating.

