### Sample Size and Power Considerations

The power analysis was performed using Emory Healthcare system retrospective data, with mortality estimates based on proportion of normal saline vs balanced crystalloids received. Usual care has an expected mortality rate of 6%, and intervention has an expected mortality rate of 3%. To detect a proportion difference (P2 – P1) of 0.03 (or P1 of 0.03) with 90% power, the number of participants needed will be 1001 in the intervention arm and 1001 in the usual care arm (Table 1). The power was computed using the tests for 2 proportions module from PASS 2023, version 23.0.1 (NCSS LLC).

**Table 1. zoi241019t1:** Power and Sample Size for Hypothesis Tests of the 30-Day Inpatient Mortality Difference Between Usual Care and Intervention^a^

Test	Sample size assumptions and results					
	Usual care P2	Intervention P1	Difference (P2 − P1)	No. of participants		Statistical power, %
				Per group	Total	
1	0.06	0.03	0.03	748	1496	80
2	0.06	0.04	0.02	1863	3726	80
3	0.06	0.03	0.03	1001	2002	90
4	0.06	0.04	0.02	2493	4986	90

^a^
The usual care group mortality rate (P2) is assumed to be 0.06. To detect a proportion difference (P2 − P1) of 0.03 (or P1 of 0.03) with 90% power, the number of participants needed will be 1001 in the intervention arm and 1001 in the usual care arm.

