### Interim Analysis

The DSMB will conduct 2 interim analyses. A focus for the interim analyses is the effectiveness of the intervention in changing clinician ordering behavior. To decrease the use of normal saline in the intervention arm, an education program for ED and ICU clinicians has occurred before trial enrollment. On both the 3- and 6-month interim analyses, if the rate of normal saline use is greater than 25%, an additional targeted education campaign will be undertaken. At both interim analyses, the DMSB will monitor for meeting a stopping boundary for efficacy, with an unadjusted primary outcome (30-day mortality) difference between groups using a χ^2^ test with a significance level of *P* < .001. The conservative Haybittle-Peto boundary is used so that the final analysis can be performed with an unchanged significance level (2-sided *P* < .05). At the 3-month interim analysis, the DSMB can suggest a sample size reestimation if the mortality rate in the usual care arm differs clinically (eg, 9% vs 6%) from the estimated 6% mortality rate. The DSMB can also suggest a sample size reestimation if the baseline prevalence of normal saline use is significantly lower than the estimated 60%.

No futility boundary to mortality difference will be applied given that even a small clinical benefit from the intervention could have a large impact given the ubiquity of crystalloid fluid therapy. In addition to prescheduled data reviews and planned safety monitoring, the DSMB may be called on for ad hoc reviews. The DSMB will review any event that potentially impacts safety at the request of the DSMB chair. The DSMB will comprise an academic intensivist from a separate university, an academic intensivist from a nonparticipating hospital in Atlanta, and an independent biostatistician.

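### The unadjusted primary test is valid but leaves a small gain in precision unused: age and SOFA at randomization, extracted for every patient, enter only the secondary model

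*Protocol article*

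**What the plan says.** All references are to the Methods of the Protocol article.

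- **Primary test** (Statistical Analysis): "The primary analysis will be an assessment for a difference in 30-day inpatient mortality between the arms", carried out "with a 2-sided *z* test with continuity correction and pooled variance". No covariate enters it.
- **Adjusted model** (same section): a mixed log-binomial regression is planned as a secondary analysis, "adjusted for baseline characteristics including age, sex, race and ethnicity, and Sequential Organ Failure Assessment (SOFA) score at randomization". It also has a random intercept for hospital (a fixed effect in a sensitivity analysis), trial month, and a month-by-treatment interaction. Covariate-adjusted mortality by arm and the adjusted difference, with 95% confidence intervals, are to be reported.
- **Allocation** (Randomization and Allocation): "in a simple 1:1 ratio without stratification".
- **Data** (Data Management, with Table 2): baseline variables are collected on every randomized patient. Age, hospital and SOFA are among the listed columns.
- **Size** (Sample Size and Power Considerations): the target is 90% power when mortality is 6% under usual care and 3% under intervention, and the article concludes that "the number of participants needed will be 1001 in the intervention arm and 1001 in the usual care arm".
- **Interim looks** (Interim Analysis): two unadjusted chi-squared looks at P < .001, so that the "final analysis can be performed with an unchanged significance level (2-sided *P* < .05").

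**The concern.** The decision rests on a comparison that uses none of the baseline information already in hand. If age and SOFA predict death, part of the variation in the outcome is explained before treatment. An estimator that removes that part has a smaller standard error for the same quantity, the marginal difference in 30-day inpatient mortality. It needs no extra patients and no extra data.

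The planned secondary model does not close the gap. It does not decide the trial. Its month-by-treatment interaction also means that its treatment coefficient, taken alone, is not one overall effect. If the two analyses were to differ, the less precise one would govern the conclusion.

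At stake is a modest amount of power. Only about 90 deaths are expected (1001 × 0.06 + 1001 × 0.03 ≈ 90), and low mortality limits how much variance any covariate can explain.

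**Working it through.** **Inputs from the article.** Mortality 6% and 3%; two-sided 5% level; 1001 per arm; pooled-variance z test with continuity correction. **Assumed input.** The prognostic strength of age plus SOFA, expressed as a C-statistic. The article gives none, so a range is shown.

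**1. Reproduce the plan's sample size (no continuity correction).** With mean mortality 0.045:

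n = [1.960·√(2·0.045·0.955) + 1.2816·√(0.06·0.94 + 0.03·0.97)]² / 0.03²
= (0.57461 + 0.37473)² / 0.0009 = 0.90125 / 0.0009 ≈ 1001.4 per arm.

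This is 1002 when rounded up, against the stated 1001. The other rows of Table 1 also reproduce to within one patient per arm. With the continuity correction the same row would need 1068, so Table 1 was computed without it.

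**2. Power at 1001 per arm, no covariates.** The null SE is √(2·0.045·0.955/1001), and 1.960 times it is 0.018162. The alternative SE is √(0.0855/1001) = 0.009242.

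- Uncorrected: Φ[(0.03 − 0.018162)/0.009242] = Φ(1.281) = 90.0%.
- With the planned correction of 1/1001 = 0.000999: Φ[(0.029001 − 0.018162)/0.009242] = Φ(1.173) = 88.0%.

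The two-point gap is the continuity correction alone. The right baseline for judging the covariates is therefore 90.0%.

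**3. Variance with covariates.** Write p₁(x) and p₀(x) for the risk of death by arm at baseline prognosis x. Per-patient large-sample variances of the marginal risk difference under 1:1 allocation are:

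- unadjusted: 2(0.06·0.94 + 0.03·0.97) = 0.171;
- standardized: 2{E[p₁(1−p₁)] + E[p₀(1−p₀)]} + Var(p₁ − p₀).

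Here x is a standard normal prognostic index on the logit scale, with intercepts set to give 6% and 3% mortality. The slopes 0.55, 0.75, 1.0 and 1.25 correspond to the C-statistics below.

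**4. Convert to power.** A variance cut r acts like 1001/(1 − r) patients per arm in the uncorrected formula. For r = 8.53%, 1001/0.9147 ≈ 1094, which gives 92.3%. The n per arm for 90% power is 1002 × (1 − r), rounded up.

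| Assumed C | Variance cut | Power at 1001 per arm | n per arm for 90% |
|---|---|---|---|
| none (unadjusted, uncorrected) | 0 | 90.0% | 1002 |
| 0.65 | 1.4% | 90.4% | 988 |
| 0.70 | 2.8% | 90.8% | 975 |
| 0.75 | 5.2% | 91.5% | 950 |
| 0.80 | 8.5% | 92.3% | 917 |

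The gain is worth 1002 − 988 = 14 to 1002 − 917 = 85 patients per arm.

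**5. Simulation check.** 1001 per arm, 4000 runs per setting, logistic working model, influence-function SE:

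| C (approx.) | Power, uncorrected z | Power, planned corrected z | Power, standardized | Type I error, standardized | Type I error, corrected z |
|---|---|---|---|---|---|
| 0.65 | 90.6% | 88.9% | 91.1% | 5.1% | 4.1% |
| 0.75 | 90.8% | 88.6% | 92.1% | 5.0% | 4.4% |
| 0.80 | 91.0% | 89.4% | 92.8% | 5.2% | 3.9% |

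The Monte Carlo standard error of a 5% rejection rate is √(0.05·0.95/4000) ≈ 0.3 points, so the adjusted test holds its level. The simulated gains over the uncorrected test (0.4 to about 1.9 points) are in line with step 4 (0.4 to 2.3 points).

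**The case against.** The strongest reply is that nothing here is wrong. An unadjusted two-proportion test is valid under simple randomization and matches the way the trial was sized. An adjusted analysis of the same outcome, with hospital terms and an adjusted risk difference, is already planned. What remains is which analysis is called primary, for a gain that could be under half a percentage point of power. All of that stands, and it is why the point is one of efficiency only.

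Three stronger readings are tempting, and the article does not support them.

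- A reader might infer that unstratified allocation leaves the primary result biased, or exposed to chance imbalance as a second harm. It does not. Chance imbalance is already in the standard error of the unadjusted test. With 1001 per arm, the standardized difference in any covariate has an SD of only √(2/1001) ≈ 0.045. Removing that component is the same variance gain described differently.
- A reader might credit adjustment with the whole step from about 88% to above 92%. About two points of it come from the continuity correction.
- A reader might take the prognostic strength of age and SOFA as established. The article gives no such figure, and this population is selected on vital signs, which could narrow the range of severity.

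Two practical objections also carry weight. SOFA is needed at the moment of a saline order in the ED, when components may be missing, and the article rules out missing data only for outcomes. A term for ED or hospital was not part of the calculations, and its value with about 90 deaths is unknown.

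Using unadjusted interim looks with an adjusted final test is not a serious obstacle. Two looks at 0.001 add at most 0.002 to the 0.05 final level, whatever the final statistic.

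**Conclusion.** The point holds as a small improvement available at little cost. The planned primary test is valid; it simply does not use information that the trial collects anyway. For an assumed C-statistic of 0.65 to 0.80, standardized adjustment for age and SOFA cuts the variance of the risk difference by about 1% to 9%. Power at 6% versus 3% and 1001 per arm rises from 90.0% to about 90.4% to 92.3%. The estimand is unchanged, and type I error in simulation was 5.0% to 5.2%.

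The size rests on the assumed prognostic strength and on the plan's own mortality rates. The planned secondary model reduces the importance of the point but does not remove it, because that model does not govern the primary conclusion and carries a treatment-by-month term.

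**What to change.** Before outcome data are unblinded, specify the primary analysis as the marginal difference in 30-day inpatient mortality obtained as follows:

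- a logistic model with treatment, age and SOFA at randomization, and no month-by-treatment interaction;
- predictions standardized over all randomized patients;
- a robust (influence-function) standard error, tested two-sided at 5%.

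Keep the unadjusted z test as the supporting analysis, keep the mixed log-binomial model as secondary, and leave both Haybittle-Peto looks unadjusted as written. A term for ED or hospital is optional. Promoting the existing secondary model unchanged is not recommended, because of its interaction term and because log-binomial fits can fail to converge.

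The cost is a change of wording, slightly more programming, and one simple prespecified rule for missing SOFA components. No new data or patients are needed. Whether to keep the continuity correction in the supporting test should be settled separately.

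### Table 1's sample sizes fit a z test without continuity correction, but the primary test applies one, so 1001 per arm gives about 88-89% power rather than 90%

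*Protocol article*

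**What the plan says.** The Statistical Analysis section names the primary test: a two-sided z "test with continuity correction and pooled variance", comparing 30-day inpatient mortality between the randomized arms by intention to treat.

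Sample Size and Power Considerations assumes 6% mortality under usual care and 3% under the intervention. For a difference of 0.03 it states that, "with 90% power, the number of participants needed will be 1001 in the intervention arm and 1001 in the usual care arm". Table 1 adds three alternatives: 748 per arm (80% power, 6% vs 3%), 1863 per arm (80%, 6% vs 4%) and 2493 per arm (90%, 6% vs 4%). The section names the PASS two-proportions module but not the test option chosen in it.

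The Interim Analysis section supplies the significance level: "the final analysis can be performed with an unchanged significance level (2-sided *P* < .05". Randomization and Allocation gives 1:1 allocation.

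**The concern.** A sample size is tied to the test it was computed for. A continuity correction shrinks the observed difference before it is compared with its standard error, so the corrected test rejects less often than the uncorrected one at the same sample size. A table computed without the correction overstates the power of a corrected primary test. The reverse also holds: keeping 90% power with the corrected test requires more patients than the table shows.

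Three things are at stake:

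- The power claimed for the primary analysis is not the power it has.
- The Interim Analysis section lets the DSMB suggest sample size re-estimation. If that is done with the method behind Table 1, the mismatch carries into the revised size.
- A borderline final result could be significant under one version of the test and not under the other. Which version governs, and which one the planning figures describe, should be settled beforehand.

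**Working it through.** **Inputs.** P2 = 0.06 and P1 = 0.03 or 0.04 (Table 1); two-sided alpha 0.05 (Interim Analysis), so z = 1.960; power 80% or 90%, so z = 0.842 or 1.282; 1:1 allocation. Write D = P2 − P1 and p̄ = (P1 + P2)/2.

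**Step 1: reproduce Table 1 (uncorrected, pooled variance).**

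n = [z_α √(2p̄(1−p̄)) + z_β √(P1(1−P1) + P2(1−P2))]² / D²

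For 6% vs 3% at 90% power: p̄ = 0.045. The first term is 1.960 × √0.08595 = 0.5746 and the second is 1.282 × √(0.0291 + 0.0564) = 0.3747. So n = (0.9493)² / 0.0009 = 1001.4.

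**Step 2: the same with the continuity correction (Fleiss).**

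n_cc = (n/4) × [1 + √(1 + 4/(nD))]²

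For the same row: 4/(1001.4 × 0.03) = 0.1331, √1.1331 = 1.0645, and n_cc = 250.3 × (2.0645)² = 1067.0.

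| Row | Stated per arm | Uncorrected, pooled | Corrected | Corrected / stated |
|---|---|---|---|---|
| 6% vs 3%, 80% | 748 | 748.4 | 813.7 | 1.088 |
| 6% vs 4%, 80% | 1863 | 1862.9 | 1961.7 | 1.053 |
| 6% vs 3%, 90% | 1001 | 1001.4 | 1067.0 | 1.066 |
| 6% vs 4%, 90% | 2493 | 2493.4 | 2592.5 | 1.040 |

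The uncorrected formula with unpooled variance gives 745.6, 1860.2, 998.2 and 2490.3. That is also close, but not to the patient. The corrected formula fits no row.

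**Step 3: power of the stated test at the stated sizes.** With equal arms the correction reduces |p̂1 − p̂2| by 1/n. By normal approximation at n = 1001:

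- reduced difference: 0.03 − 0.000999 = 0.029001
- critical difference: 1.960 × √(0.08595/1001) = 0.018162
- standard error under the alternative: √(0.0855/1001) = 0.009242
- power: Φ[(0.029001 − 0.018162)/0.009242] = Φ(1.173) = 0.880

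Exact power sums the binomial probabilities of all pairs of death counts for which the test rejects.

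| Per arm | Stated power | Corrected, approx. | Corrected, exact | Uncorrected, exact |
|---|---|---|---|---|
| 748 | 80% | 76.3% | 77.1% | 80.9% |
| 1863 | 80% | 77.8% | 78.2% | 80.3% |
| 1001 | 90% | 88.0% | 88.7% | 90.7% |
| 2493 | 90% | 88.8% | 89.0% | 90.2% |

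By exact enumeration, the corrected test at 6% vs 3% first reaches 90% at 1043 per arm and 80% at 798 per arm.

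**Step 4: type I error at 1001 per arm (exact, two-sided).** With the correction it is 3.7%, 3.9% and 4.0% at common event rates of 3%, 4.5% and 6%. Without it, it is 5.0% at all three.

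**The case against.** The strongest reply is that the effect is small where it counts. At the adopted design the exact shortfall is 1.3 points. With about 90 deaths in total, the correction raises the between-arm difference needed for significance by one death, from about 18.2 to 19.2. The larger miss, at 748 per arm, is in a row the trial did not adopt. A prespecified conservative test is not invalid, and it leaves a little room for the two interim looks. All of this stands, and it limits the severity. It does not make the stated power correct for the stated test.

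Other points also stand in part:

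- Omission of the correction is inferred from the numbers, because the article does not name the PASS option. The unpooled uncorrected formula also comes within three patients per arm. But no corrected version fits any row.
- The corrected sizes in the table above are Fleiss approximations. At 6% vs 3% and 90% power the gap is about 66 per arm on that formula (1067.0 against 1001) and 42 by exact enumeration (1043 against 1001).
- The interim test is described only as a χ² test, with no word on correction. That dropping the correction would align the final and interim tests is therefore likely, but not established.
- Removing a correction makes the primary test less conservative, which is a more delicate change once a trial is running than restating a power figure.

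This is not a detail left to a fuller document: the article states both the test and the sample size, and they do not match.

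**Conclusion.** Wrong as written. Table 1 describes an uncorrected z test, while the primary analysis is a corrected one. For the stated test, 1001 per arm gives 88.7% power by exact calculation (88.0% by approximation) instead of 90%, and the other three rows also fall short, by 1.0 to 2.9 points exactly. The correction brings the actual type I error down to 3.7-4.0%. At this sample size the uncorrected test already holds 5.0%, so the correction is not needed to protect the level.

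The result rests on the article's own rates, 1:1 allocation and two-sided alpha of 0.05, treats patients as independent, and evaluates the final test without the interim looks. The validity of the primary result is not threatened. It should be corrected because it concerns the headline power claim and is cheap to put right.

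**What to change.** Choose one of the following:

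1. **Drop the correction.** Name the uncorrected pooled z test (equivalent to the Pearson chi-square test) as the primary test. Table 1 then stands as printed. If enrollment has begun, record this as a dated amendment made without knowledge of outcomes by arm.
2. **Keep the correction.** State that Table 1 was computed without it and restate the power at the existing sizes: about 88-89% at 1001 per arm, 76-77% at 748, 78% at 1863 and 89% at 2493.

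In either case, name the test variant behind Table 1, say whether the interim χ² test is corrected, and use the same variant in any sample size re-estimation. The cost is one phrase in Statistical Analysis or one column in Table 1, plus a clarifying sentence. Neither option needs more patients. Holding 90% with the corrected test would take about 42 (exact) to 67 (Fleiss, rounded up to 1068) more per arm.
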